## Abstract

**Introduction:**

Sepsis is a major cause of death among hospitalised patients. Accumulating evidence suggests that immune response during sepsis cascade lies within a spectrum of dysregulated host responses. On the one side of the spectrum there are patients whose response is characterised by fulminant hyperinflammation or macrophage activation-like syndrome (MALS), and on the other side patients whose immune response is characterised by immunoparalysis. A sizeable group of patients are situated between the two extremes. Recognising immune endotype is very important in order to choose the appropriate immunotherapeutic approach for each patient resulting in the best chance to improve the outcome.

**Methods and analysis:**

ImmunoSep is a randomised placebo-controlled phase 2 clinical trial with a double-dummy design in which the effect of precision immunotherapy on sepsis phenotypes with MALS and immunoparalysis is studied. Patients are stratified using biomarkers. Specifically, 280 patients will be 1:1 randomly assigned to placebo or active immunotherapy as adjunct to standard-of-care treatment. In the active immunotherapy arm, patients with MALS will receive anakinra (recombinant interleukin-1 receptor antagonist) intravenously, and patients with immunoparalysis will receive subcutaneous recombinant human interferon-gamma. Τhe primary endpoint is the comparative decrease of the mean total Sequential Organ Failure Assessment score by at least 1.4 points by day 9 from randomisation.

**Ethics and dissemination:**

The protocol is approved by the German Federal Institute for Drugs and Medical Devices; the National Ethics Committee of Greece and by the National Organization for Medicines of Greece; the Central Committee on Research Involving Human Subjects and METC Oost Netherland for the Netherlands; the National Agency for Medicine and Medical Products of Romania; and the Commission Cantonale d’éthique de la recherche sur l’être human of Switzerland. The results will be submitted for publication in peer-reviewed journals.

**Trial registration number:**

NCT04990232.

STRENGTHS AND LIMITATIONS OF THIS STUDYImmunoSep is a double-blinded randomised phase 2 clinical trial with double-dummy, placebo-controlled design.This is a personalised medicine study to demonstrate the effects of immunotherapy tailored to specific immune endotypes.The primary endpoint is the decrease of mean Sequential Organ Failure Assessment score by day 9.ImmunoSep also aims for the identification of novel biomarkers through the integrative analysis of -omics of patients’ samples.This trial is not powered to demonstrate an effect on mortality.

## Introduction

Sepsis is a life-threatening organ dysfunction that results from the dysregulated host response to an infection.^1^ Patients with sepsis-induced dysregulation present a broad spectrum of perturbation ranging from immune hyperactivation to immune suppression. In this respect, approximately 5%–10% of patients present mainly with fulminant hyperinflammation, an entity also known as macrophage activation-like syndrome (MALS),^2^ whereas a sizeable minority of other patients have mainly ineffective responses to secondary infections, a condition described as immunoparalysis.^3^

There is accumulating evidence that delivery of targeted immunotherapy for patients who present with these two extremes may improve outcome. Indeed, the post-hoc analysis of a randomised clinical trial (RCT) conducted more than 25 years ago showed that treatment with anakinra, the recombinant antagonist of the interleukin (IL)-1 receptor, provided 30% decrease of 28-day mortality among patients with hepatobiliary dysfunction and disseminated intravascular coagulation who bear phenotypical characteristics compatible with MALS.^4^ During the last years, we have suggested that serum ferritin can be an important diagnostic tool for MALS. Studying 5121 patients who were split into one test and into one validation cohort and studying another confirmation cohort from Sweden, it has been found that serum concentrations of ferritin greater than 4420 ng/mL had specificity 97.1% and 98% negative predictive value for the classification of MALS.^2^

On the other hand, the decrease of the expression of the human leucocyte antigen (HLA)-DR expression on the membrane of circulating monocytes is considered one of the hallmarks of immunoparalysis resulting in a dysfunctional immune response, which in turns leads to susceptibility for secondary infections, prolonged hospitalisation and increased mortality.^5^ The presence of immunoparalysis in patients with sepsis is associated with at least 50% risk of death in the subsequent 28 days.^6^ Evidence from human volunteers subjected to an endotoxin challenge suggests that immunoparalysis can be reversed by recombinant human interferon-gamma (rhIFNγ).^7^ In addition, when rhIFNγ was administered in nine patients with septic shock, reversal of immunoparalysis was also achieved.^8^

Based on the existing evidence, experts from five European countries (Germany, Greece, the Netherlands, Romania and Switzerland) designed a double-blind, double-dummy RCT with the aim to deliver personalised immunotherapy as adjunctive treatment to standard of care. The acronym of the trial is ImmunoSep (EudraCT number: 2020-005768-74; ClinicalTrials.gov NCT04990232) and it is funded by the Horizon 2020 programme of the European Union.

### Objectives

ImmunoSep is a randomised placebo-controlled phase 2 clinical trial with a double-dummy design in which the effect of personalised immunotherapy in patients with sepsis and either MALS or immunoparalysis is studied. Τhe primary hypothesis is that the efficacy of immunotherapy in sepsis depends on the specific immune endotype of each patient, and patient stratification for administration of adjunctive immunotherapy aiming to reverse MALS and sepsis-induced immunoparalysis improves chances for a better outcome when compared with a one-size-fits-all immunotherapy approach. It is anticipated that organ dysfunctions as expressed by the mean SOFA (Sequential Organ Failure Assessment) score will be improved by day 9 after randomisation.

## Methods and analysis

### Study design and setting

ImmunoSep is a prospective randomised placebo-controlled phase 2 clinical trial in a total number of 24 academic and non-academic study sites in Greece, Germany, Switzerland, the Netherlands and Romania aiming to assess whether personalised adjunctive immunotherapy directed against a state of either fulminant hyperinflammation or immunoparalysis is able to improve sepsis outcomes. Patients will be selected by a panel of biomarkers and laboratory findings and will be allocated to placebo or immunotherapy treatment according to their needs by 1:1 ratio. The study enrolment will be competitive between the participating study sites targeting 280 participants.

### Study population

Inclusion and exclusion criteria determining the eligibility of study participants are reported in box 1.

Box 1Inclusion and exclusion criteria of the ImmunoSep trialInclusion criteria (patients should meet ALL of them)Age equal to or above 18 years.Both genders.In case of women, unwillingness to become pregnant during the study period; birth control measures apply.Written informed consent provided by the patient or by one first-degree relative/spouse in case of patients unable to consent.Community-acquired pneumonia or hospital-acquired pneumonia or ventilator-associated pneumonia or primary bacteraemia (bloodstream infection (BSI)).Sepsis defined by the Sepsis-3 definitions.Patients with signs of macrophage activation-like syndrome or sepsis-associated immunoparalysis.Time from classification into sepsis by the Sepsis-3 definitions and start of blind intervention less than 72 hours.Exclusion criteria (patients meeting ANY of the following criteria CANNOT be enrolled)Age below 18 years.Refusal of written informed consent.Acute pyelonephritis or intra-abdominal infection, meningitis or skin infection.Any stage IV malignancy.Neutropenia defined as an absolute neutrophil count lower than 1500/mm^3^.Any ‘do not resuscitate’ decision in the hospital.In the case of BSI, patients with blood cultures growing coagulase-negative staphylococci or skin commensals or catheter-related infections cannot be enrolled.Active tuberculosis (TB) as defined by the co-administration of drugs for the treatment of TB.Infection by the HIV.Any primary immunodeficiency.Oral or intravenous intake of corticosteroids at a daily dose equal to 0.4 mg/kg prednisone or greater for more than the last 15 days.Any anti-cytokine biological treatment the last 1 month.Medical history of systemic lupus erythematosus.Medical history of multiple sclerosis or any other demyelinating disorder.Pregnancy or lactation. Women of childbearing potential will be screened by a urine pregnancy test before inclusion in the study.

### Study procedures

Patients eligible for the study are patients either admitted to hospital from the emergency department or patients already hospitalised in the general clinical wards or in intensive care units. Once a patient is presenting with at least two of the signs of the systemic inflammatory response syndrome or at least one point of the quick SOFA score, then he/she or a legal representative in case the patient cannot consent, is asked for written informed consent. Trial procedures and flow are summarised in figure 1. When the patient does not meet any exclusion criteria, he/she is screened for the presence of lower respiratory tract infection (community-acquired pneumonia, hospital-acquired pneumonia or ventilator-associated pneumonia) or primary bacteraemia and for the Sepsis-3 definition.^1^ If the patient meets all these inclusion criteria, the patient is then screened for MALS and immunoparalysis. For this, whole blood is drawn for the measurement of ferritin by an enzyme immunosorbent assay, and for the expression of HLA-DR molecules on CD14+ CD45+ monocytes using the Quantibrite assay by flow cytometry (BD Biosciences, New Jersey, USA). Screened patients will be classified into three groups of immune-endotypes: (a) MALS when serum ferritin is more than 4420 ng/mL irrespective of the number of HLA-DR molecules on circulating CD14+ CD45+ monocytes; (b) immunoparalysis when serum ferritin is 4420 ng/mL or lower and the number of HLA-DR molecules on circulating CD14+ CD45+ monocyte is less than 5000; and (c) unclassified when serum ferritin is 4420 ng/mL or lower and the number of HLA-DR molecules on circulating CD14+ CD45+ monocytes is 5000 or more. If a patient meets the criteria for both MALS and immunoparalysis, MALS is considered as the dominant diagnosis due to the higher mortality in this condition. Patients of immunogroups (a) and (b) may be enrolled in the trial provided they meet the time difference of less than 72 hours from onset of sepsis.

**Figure 1 F1:**
[figure not shown]
Screening process for patient eligibility for enrolment in the ImmunoSep Study. HLA, human leucocyte antigen.

Study screening is facilitated by the generated web platform at the address https://sepsisonline.org. Investigators blinded to the study intervention enter the data on the inclusion and exclusion criteria in the platform and then the screened patient receives a code. Blinded investigators do not have access to the laboratory results of classification into immunogroups. These laboratory results are sent by an email to the unblinded investigators. Once the unblinded investigators receive the email, they enter the results of ferritin and HLA-DR on the platform and they receive immediate notification if the patient is enrolled or not and, in case of enrolment, of the immunogroup (MALS, sepsis-induced immunoparalysis) and if the patient is allocated to placebo or active treatment. Separate secure usernames and passwords are generated for every blinded and unblinded investigator permitting restricted access to the platform fields according to their role in the study.

### Study intervention/allocation to blind treatment

The unblinded pharmacists receive information on the daily preparation of the study drug by the site https://sepsisonline.org where they have to log-in using a secure username and password. Once a patient is considered eligible for enrolment, he will be allocated blindly 1:1 to one of the two groups of treatment. The randomisation is stratified by study site and it is done using one computer-generated sequencing. The preparation of the study drug will be done in each study site by the unblinded pharmacist investigators. The two groups of treatment are:

**Placebo**. In addition to standard-of-care treatment decided by the attending physicians, patients will also receive intravenously 20 mL (10 mL for patients when creatinine clearance is lower than 30 mL/min) 0.9% saline (N/S) three times a day (every 8 hours) for 15 days and 0.5 mL subcutaneously 1 mL 0.9% N/S every other day for a total of 15 days.**Active immunotherapy**. In addition to standard-of-care treatment decided by the attending physicians, patients with MALS will receive 200 mg anakinra every 8 hours and subcutaneous placebo as specified above, whereas patients with immunoparalysis will receive intravenous placebo as specified above and subcutaneous 100 µg rhIFNγ once every other day for a total of 15 days. Creatinine clearance should be calculated daily by the Cockcroft Gault equation and when it is lower than 30 mL/min, anakinra will be given at half dose.

### Blinding protocol

The preparation of the study drug will be done in each study site by the unblinded pharmacist investigators. Syringes with active drug or placebo will be covered to conceal the identity of the test article. The unblinded pharmacist will provide the covered syringes to the blinded nurse or blinded investigator who will administer the infusion. All other subinvestigators and the patients are blinded to the assigned intervention.

### Study procedures

An overview of all study procedures is provided in table 1. Briefly, visits 1–15, visit 21, visit 28 and visit 90 include recording of co-administered drugs; SOFA score; vital signs; absolute blood cell count and differentiation, haemoglobin and absolute platelet count (if available); biochemistry (if available); coagulation (if available); blood gasses (if available), microbiology and antibiogram (if available). There would also be recording of the clinical state of the infection making the patient eligible for the study. Of utmost importance is recording and subsequently properly reporting any adverse event/serious adverse event occurring during trial participation. At visit days 1, 2, 4, 7, 15, 21, 28 and 90, blood sampling for trial-related purposes is drawn (transcriptomic, flow cytometry, cytokine production, ATAC-epigenome sequencing, proteomic analysis) and microbiome samples from nares, oral cavity and rectum. All collected samples are pseudoanonymised using a 9-digit code. Separate coding is done per study site.

**Table 1 T1:** Study visits

Day	Study visits																		
	0	1	2	3	4	5	6	7	8	9	10	11	12	13	14	15	21	28	90
Obtain ICF	X																		
Study drug		X	X	X	X	X	X	X	X	X	X	X	X	X	X	X			
SOFA score		X	X	X	X	X	X	X	X	X	X	X	X	X	X	X	X		
Medical history		X																	
Clinical state of infection							X	X	X	X	X	X	X	X	X	X	X		
Survival		X	X	X	X	X	X	X	X	X	X	X	X	X	X	X	X	X	X
Vital signs		X	X	X	X	X	X	X	X	X	X	X	X	X	X	X	X		
Lab tests		X	X	X	X	X	X	X	X	X	X	X	X	X	X	X	X		
Microbiology		X	X	X	X	X	X	X	X	X	X	X	X	X	X	X	X		
Blood collection		X	X		X			X								X	X	X	X
Microbiome samples		X	X		X			X								X	X	X	X
Co-administered medication		X	X	X	X	X	X	X	X	X	X	X	X	X	X	X	X		
Adverse events			X	X	X	X	X	X	X	X	X	X	X	X	X	X	X	X	X

ICF, informed consent form; SOFA, Sequential Organ Failure Assessment.

### Study endpoints

The primary efficacy endpoint is the difference in the mean total SOFA score until day 9 after randomisation between the two groups of treatment. The time frame of 9 days for the assessment of the primary endpoint is based on previous experience coming from the VISEP^9^ and MAXSEP^10^ RCTs where this endpoint was used to assess an impact of treatment on sepsis-induced organ dysfunction at day 9.

The secondary study endpoint is the comparison of the two groups of treatment on: (a) 28-day all-cause mortality; (b) 90-day all-cause mortality; (c) the mean total SOFA score on day 15 from randomisation; (d) the impact of personalised immunotherapy on the reversal of MALS or immunoparalysis on day 15 from randomisation, defined for patients with MALS as at least 15% decrease of the baseline serum ferritin, and for patients with immunoparalysis as restoration of HLA-DR expression on CD45/CD14 monocytes above 8000/cell. The assessment of the mean total SOFA score on day 15 from randomisation is a read-out of treatment efficacy at the end of treatment. It is considered that a later time point of assessment of the mean total SOFA score is not needed since mortality is the secondary endpoint already assessed at a later time point.

Exploratory study endpoints are: (a) the impact of personalised immunotherapy on the resolution of infection leading to study enrolment on day 15 after randomisation; and (b) the development of genomic, epigenomic, proteomic, metabolomic and microbiomic surrogate biomarkers for the primary and secondary endpoints. This will come from the exploitation of the genomic and proteomic material that will be analysed by the partners of the ImmunoSep Project.

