### Statistical analysis

The endpoints of the change of the mean SOFA score will be compared between the two groups of treatment using the Welch’s t-test for mean differences. The endpoints of time to an event will be analysed using Cox regression analysis. Analysis will be done in the intention-to-treat population with sensitivity analysis for the per-protocol population. Missing values will be imputed by last observation carried forward.

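### The day-15 criterion for reversal of MALS lets any patient with baseline ferritin above 5200 ng/mL count as reversed while still meeting the trial's own MALS definition, and the carry-forward rule makes no exception for death

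*Protocol article*

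**What the plan says.** All references are to the protocol article.

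- **Entry, MALS** (Study procedures, screening part): "MALS when serum ferritin is more than 4420 ng/mL irrespective of the number of HLA-DR molecules". Ferritin alone decides this classification.
- **Entry, immunoparalysis** (same section): ferritin at or below 4420 ng/mL, and "the number of HLA-DR molecules on circulating CD14+ CD45+ monocyte is less than 5000".
- **Secondary endpoint (d)** (Study endpoints): the two arms are compared on "reversal of MALS or immunoparalysis on day 15 from randomisation". For MALS, reversal is "at least 15% decrease of the baseline serum ferritin". For immunoparalysis it is "restoration of HLA-DR expression on CD45/CD14 monocytes above 8000/cell".
- **Missing data and population** (Statistical analysis): "Missing values will be imputed by last observation carried forward", and "Analysis will be done in the intention-to-treat population with sensitivity analysis for the per-protocol population". Neither sentence makes an exception for death or for a particular endpoint.
- **Sampling** (Study procedures, visit part, and Table 1): trial blood is drawn on days 1, 2, 4, 7 and 15 up to this endpoint. The assays listed include flow cytometry; ferritin is not named.

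**The concern.** The trial's premise is that treatment directed at the endotype corrects it and thereby improves outcome. Among the primary and secondary endpoints, only (d) tests the first half of that premise. For MALS, the entry rule is an absolute level and the reversal rule is a relative change, and nothing links the two. A patient can pass the reversal rule and still be classifiable as MALS by the rule used at enrolment, so a favourable result on (d) would not by itself show that MALS had resolved. The article gives no reason for choosing 15%.

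Death adds a second difficulty. The Introduction cites a 28-day risk of death of at least 50% in immunoparalysis, and Study procedures describes mortality in MALS as higher, so deaths before day 15 will not be rare. As written, those patients stay in the analysis and are classified by their last available value.

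**Working it through.** The article states no reversal rate or power for this endpoint, so there is no figure to reproduce.

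**Step 1: where the two ferritin rules part.** Inputs: MALS if ferritin > 4420 ng/mL; reversed if day-15 ferritin ≤ 0.85 × baseline. A patient can be reversed and still above the cut-off only if 0.85 × baseline > 4420, that is, baseline > 4420/0.85 = 5200 ng/mL. The fall needed to reach 4420 is 1 − 4420/baseline. The baselines below are illustrations.

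| Baseline (ng/mL) | After a 15% fall | Still above 4420? | Fall needed to reach 4420 |
|---|---|---|---|
| 5,000 | 4,250 | no | 11.6% |
| 5,200 | 4,420 | no | 15.0% |
| 6,000 | 5,100 | yes | 26.3% |
| 8,000 | 6,800 | yes | 44.8% |
| 10,000 | 8,500 | yes | 55.8% |
| 20,000 | 17,000 | yes | 77.9% |

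For baselines between 4420 and 5200 the 15% rule is the stricter of the two: such a patient must fall further than the cut-off.

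**Step 2: how many patients could be affected.** This needs a baseline distribution and a distribution of change, and the article gives neither. Assumptions: Pareto baseline above 4420, with the median varied; log-normal ratio of day-15 to baseline ferritin, with median fall 0% to 70% and log-SD 0.5 or 0.8. With shape a = ln 2 / ln(median/4420), the share with baseline above 5200 is 0.85^a. The last column is simulated and shows the range over the assumed changes.

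| Assumed median baseline (ng/mL) | Share with baseline > 5200 | Share of reversed patients still > 4420 |
|---|---|---|
| 4,800 | 26% | 0–6% |
| 5,200 | 50% | 3–18% |
| 6,000 | 69% | 11–37% |
| 8,000 | 83% | 27–58% |
| 10,000 | 87% | 37–67% |
| 15,000 | 91% | 50–76% |

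The Sample size section expects 40% of patients to have MALS: 0.40 × 280 = 112, or 56 per arm.

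**Step 3: death before day 15.** Take a death on day 10 under the carry-forward rule as written.

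- Ferritin re-measured on day 7, baseline 10,000, day-7 value 8,400: the fall is 1 − 8,400/10,000 = 16%, so the patient counts as reversed on day 15.
- No ferritin after baseline: the baseline is carried forward, the fall is 0%, and the patient counts as not reversed.
- The same logic holds for HLA-DR: a day-7 value above 8000 per cell is carried to day 15.

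The article gives no day-15 mortality. If 20% to 40% of MALS patients had died by then (an assumption), 0.20 × 56 ≈ 11 to 0.40 × 56 ≈ 22 per arm would be classified by a carried-forward value. That is the number exposed to the rule, not the number it would turn into reversals.

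**The case against.** Several points on the other side carry weight.

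- **A reader might infer that most patients counted as reversed still have MALS.** The article does not support this. Even the weaker statement, that most MALS patients could be in that position, needs a median baseline above 5200 ng/mL under the distribution assumed here. The share of reversed patients actually still above 4420 runs from about 0% to 76% over the assumptions tried.
- **The point about death is conditional.** Ferritin is not named among the assays on the interim blood draws. If it is measured only at baseline and day 15, carrying forward classifies the dead as not reversed. Flow cytometry is listed, so interim HLA-DR is plausible, but the schedule does not say so. The carry-forward sentence is one general line in a condensed article, and an analysis plan that is not shown may treat death separately. What stands is that the rule, as stated, has no exception.
- **A reader might go on to say that carrying forward favours the arm with more deaths.** That is not shown. It would require early values in patients who die to pass the criterion more often than day-15 values in survivors. Nor is there a figure for how often placebo patients would pass the 15% bar.
- **The HLA-DR rule is not an error.** Entry below 5000 and restoration above 8000 leave a margin beyond the entry cut-off, which is a legitimate design choice. It does mean that reversal is held to different standards in the two endotypes, which is a reason to report them separately.
- **4420 ng/mL is supported in the Introduction as a classification cut-off, not as a response criterion.** A cut-off alone would also be a poor substitute, since 4421 to 4419 would then count as reversal. This argues for requiring both conditions, not for leaving the ceiling out.

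**Conclusion.** The definitional gap stands, and it follows from the article's own two rules without any assumption: above a baseline of 5200 ng/mL, reversal and continuing MALS are compatible. How often this would occur is unknown.

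The carry-forward rule, read as written in the intention-to-treat population, lets a patient who dies before day 15 count as reversed. This holds only if the biomarker was re-measured after baseline, the last value met the criterion, and no unseen plan overrides the rule.

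Both matters concern what the article fixes, not what it leaves out. Their reach is limited to secondary endpoint (d). The change is worth making because of what that endpoint is meant to show.

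**What to change.** - Define reversal of MALS as being alive on day 15 with **both** a ferritin fall of at least 15% from baseline **and** ferritin at or below 4420 ng/mL. The fall required is then the larger of 15% and 1 − 4420/baseline, so nothing changes for baselines up to 5200.
- Count death before day 15 as non-reversal in both endotypes, and do not apply last observation carried forward to deaths for this endpoint.
- Report reversal separately for MALS and immunoparalysis, and keep the 15% fall alone as a supportive result for MALS.

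The cost is a change of endpoint wording. Day-15 blood is already scheduled in Table 1, so no extra visit is needed. The reversal rate will be lower than under the 15% rule, most of all in patients with very high baselines (a 77.9% fall is needed from 20,000 ng/mL); the supportive result keeps their partial responses visible. The Discussion reports 65 patients already enrolled by 1 June 2022, so the change should be documented before treatment allocation is unblinded.
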